## Abstract

**Background:**

Prior studies demonstrate associations between risk factors for obesity and related chronic diseases (e.g., cardiovascular disease) and features of the built environment. This is particularly true for rural populations, who have higher rates of obesity, cancer, and other chronic diseases than urban residents. There is also evidence linking health behaviors and outcomes to social factors such as social support, opposition, and norms. Thus, overlapping social networks that have a high degree of social capital and community cohesion, such as those found in rural communities, may be effective targets for introducing and maintaining healthy behaviors.

**Methods:**

This study will evaluate the effectiveness of the Change Club (CC) intervention, a civic engagement intervention for built environment change to improve health behaviors and outcomes for residents of rural communities. The CC intervention provides small groups of community residents (approximately 10–14 people) with nutrition and physical activity lessons and stepwise built environment change planning workshops delivered by trained extension educators via in-person, virtual, or hybrid methods. We will conduct process, multilevel outcome, and cost evaluations of implementation of the CC intervention in a cluster randomized controlled trial in 10 communities across two states using a two-arm parallel design. Change in the primary outcome, American Heart Association’s Life’s Simple 7 composite cardiovascular health score, will be evaluated among CC members, their friends and family members, and other community residents and compared to comparable samples in control communities. We will also evaluate changes at the social/collective level (e.g., social cohesion, social trust) and examine costs as well as barriers and facilitators to implementation.

**Discussion:**

Our central hypothesis is the CC intervention will improve health behaviors and outcomes among engaged citizens and their family and friends within 24 months. Furthermore, we hypothesize that positive changes will catalyze critical steps in the pathway to improving longer-term health among community residents through improved healthy eating and physical activity opportunities. This study also represents a unique opportunity to evaluate process and cost-related data, which will provide key insights into the viability of this approach for widespread dissemination.

**Trial registration:**

ClinicalTrials.gov: NCT05002660, Registered 12 August 2021.

**Supplementary Information:**

The online version contains supplementary material available at 10.1186/s12889-022-13653-4.

## Background

Nearly 70% of U.S. adults are overweight or obese [1], and with this comes a multitude of consequences, including increased risk for several types of cancer [2, 3], diabetes [4], and cardiovascular disease [5]. Only 20% of US adults meet physical activity (PA) guidelines [6]. Inadequate PA increases risk for many chronic conditions, including some types of cancer, obesity, metabolic syndrome, and hypertension [7]. Adding as little as 10–15 min per day of PA or reducing sedentary time by 0.5 to 1 h per day confers significant health benefits, including improving biomarkers of chronic disease and reducing all-cause mortality risk [8–11]. Likewise, consuming a healthy diet, including adequate amounts of fruits and vegetables (FV), is associated with lower risk of cancer and obesity [12]; yet only about 10% of U.S. adults meet FV intake recommendations [13]. Increasing FV intake by as little as one serving per day significantly decreases all-cause mortality risk [14]. Inadequacies in PA and FV intake are major contributors to healthcare expenditure [15, 16]. This is particularly relevant for rural populations, who tend to have higher rates of cancer, obesity, physical inactivity, and poor diet than urban residents [17–21]. Rural areas also have higher rates of poverty [22] and more limited access to healthcare [23], healthy food [24], PA facilities [25], and active transportation opportunities [26]. Thus, effective and feasible interventions are needed to increase and enhance rural healthy eating and PA opportunities.

Previous evidence has shown an association between built environment features and cancer, obesity, and related health behaviors, including PA and dietary patterns [27–30]. Similarly, changes in built environment features and policies have shown potential to improve health [31–38]. Both the Centers for Disease Control and Prevention and the World Health Organization acknowledge the health impact of the environments in which people interact and recommend making changes to these environments to help people lead healthier lives [39, 40]. In their 2018 report, the National Association of County and City Health Officials suggested integrating support for policy, systems, and environmental interventions that promote health equity in cancer prevention and control planning at the local level [41]. Rural built environments often pose unique challenges, including active transport challenges (e.g., poor pedestrian infrastructure, high speed limits, lack of bike lanes) and long distances to healthy food and PA opportunities [42]. Thus, opportunities to intervene at the built environment and policy levels to encourage healthy eating and active living in rural communities are essential.

Additionally, it is increasingly understood that social environments have an influence on PA and dietary behaviors in a variety of ways, including social support/opposition, norms, and access to resources [43–47]. Yet the influence of social factors such as social capital, community cohesion, and collective efficacy on behavior change in rural populations is inadequately understood. Social networks and norms of self-help and reciprocity are often characterized as positive aspects of rural life [48]. Further, highly connected networks may speed the diffusion of behavioral changes that require strong social reinforcement [49, 50]. On the other hand, in small, isolated communities, entrenched sociocultural norms can limit people’s behavioral choices [51, 52]. Social dynamics are therefore likely to affect outcomes related to policy or built environment changes. Some studies in rural areas have focused on social-environmental determinants of health behavior change, highlighting facilitators in the social (e.g., accountability, support) and community (e.g., norms, access) domains and related barriers (e.g., social: family responsibilities, discouragement from others; community: lack of FV access, built environments unconducive to PA) [53–57].

Civic engagement interventions for built environment change, or CEBEC, is an approach that accounts for social contexts and has environmental change as a major focus. It therefore represents a novel and promising approach for promoting behavior change in the rural context. The CEBEC approach rests on civic engagement, defined as “individual and collective actions designed to identify and address issues of public concern” [58]. Civic engagement is inclusive of community volunteerism, which has been linked with positive influences on health behaviors in rural populations [59–68]. In the CEBEC approach groups of citizens are guided through a process of assessing their communities identifying issues and developing and enacting a plan for built environment change. The Change Club (CC) intervention was designed as a CEBEC intervention for rural communities. In this intervention a small group of residents (CC members [CCM]) will work to catalyze change in their community environment relative to food (for example foods in restaurants or schools) or PA opportunities (for example parks or walking trails) by following a stepwise process facilitated by an extension educator.

The theoretical framework for the CEBEC approach rests on Social Cognitive Theory [69] nested within a socioecological framework [70]. At the individual level, civic engagement is designed to promote behavioral skills, including self-regulation, by guiding CCM through a process that includes goal setting and monitoring. It is also designed to positively impact cognitive influences. Self-efficacy may be enhanced since the community project is integrated with diet and PA content that promotes small, achievable changes. At the group level, by identifying and making changes to environmental factors that affect community health, CCM will benefit by gaining a sense of collective efficacy to create cooperative change, which impacts health behaviors [71]. The groups themselves are designed to provide social support, which positively affects health behaviors [72, 73].

The CC intervention is also designed to impact the broader social environment by enhancing bonds of trust and identity as groups work together and with their communities. Because they will choose from a menu of evidence-based community-change strategies, CCM will be able to identify and tailor projects to be reasonably compatible with existing social norms. This is essential for individual- and community-level health behavior change [74], especially in the rural context. There is fairly strong evidence that eating and other health behaviors are transmitted through social networks, via observation/modeling, social rewards, and other mechanisms [75, 76]. It is expected that members of the CCM’s social networks will be impacted as CCM make changes in their own diet and PA behaviors. At the community level, civic engagement provides a potentially powerful way to impact environmental influences on behavior, not just for CCM but also for friends and family members in broader social networks, as well as other community residents who may be impacted by built environment and policy changes. Finally, particularly for CCM, behavior change may be further enhanced via reciprocal determinism, or a positive, reinforcing interaction among behavioral, cognitive, and environmental factors [69].

In previous studies, both rural and urban CEBEC interventions have led to meaningful built environment and policy changes (e.g., allocation of government funds for built environment improvements, sidewalk repair programs, addition of shade trees to encourage walking, and installation of pedestrian flashing light signals) [59–62, 77–81]. However, few studies have evaluated individual-level health behavior or health outcome changes in response to CEBEC projects. Additionally, CEBEC interventions have not been evaluated using well-matched control communities [60, 63–66]. Given the potential of this approach, and current gaps within research to date, there is a need to evaluate rural CEBEC interventions aimed at improving diet and PA. The central hypothesis is that our CEBEC intervention approach, CC, will improve health behaviors and outcomes among engaged residents and their friends and family members, and that these changes can catalyze critical steps in the pathway to improving rural health equity through improved healthy eating and PA opportunities. Thus, the overall objectives of this study are to not only address the knowledge gap but to facilitate built environment change by conducting a cluster randomized controlled trial to test whether or not CC a) improves individual health behaviors by increasing FV consumption and PA opportunities and b) promotes social cohesion and builds social trust among CCM, their friends and family members, and community residents; and to c) examine barriers to implementation and cost and d) examine maintenance of individual and collective changes. Furthermore, our study will facilitate collection of cost data and process evaluation measures to identify effective and cost-effective strategies for dissemination.

### Study aims

#### Aim 1

To evaluate changes in American Heart Association’s Life’s Simple 7 (LS7) composite cardiovascular health score and its components (see Table 3) among residents of CC intervention communities (CCM, friends and family members, and community residents) compared to comparable groups in control communities.

#### Aim 2

To evaluate changes in individual health outcomes (e.g., BMI) and behaviors (e.g., PA levels) as well as adherence to cancer-related recommendations (i.e. World Cancer Research Fund/American Institute for Cancer Research composite score [12]) among residents of CC intervention communities relative to residents of control communities.

#### Aim 3

To evaluate changes at the social/collective level (e.g., social cohesion, social engagement) as well as social network influence on outcomes in CC intervention communities relative to control communities.

#### Aim 4

To examine barriers and facilitators to implementation of the CC including costs and unintended consequences.

#### Aim 5

To examine maintenance of any observed net changes in individual or social/collective measures between CC intervention and control communities.

## Methods

This study will evaluate the effectiveness of the CC intervention in a cluster randomized controlled trial, in which communities are the clusters, using a two-arm parallel design. Cluster randomization was needed because the intervention aims to influence the community environment for healthy eating and PA as well as individual health behaviors and outcomes. We chose a parallel design for statistical efficiency; this is based on the 24-month follow-up data needed to adequately assess CC impacts and the small interclass correlations within towns (0.02–0.04) observed in our previous community randomized studies, which show that the clusters are quite homogenous. Annual longitudinal data will be collected at baseline, + 12, + 24, and + 36 months. Data collected at 24-month follow-up will provide the primary outcome analysis, and data collected at 36 months allow for the examination of maintenance of any observed changes.

### Communities

The study will be carried out in ten paired communities in two states (four in New York and six in Texas). These communities are rural per the Rural–Urban Commuting Area version 2.0 definition [20, 82] and are designated as medically underserved areas and/or Health Professional Shortage Areas [83]. Randomization (based on random numbers computer-generated by research staff) will occur after baseline measurements are collected in both communities within a pair, with five communities starting the CC process and resident-led implementation activities directly after randomization and the remaining five communities serving as controls. It is not feasible to conceal assignment to intervention or control from participants or research staff due to the nature of the design; however, field staff involved in intervention delivery will not be involved in assessing outcomes. At the conclusion of data collection (36 months after baseline), the five control communities will be provided with intervention materials, but their outcomes will not be measured after that time point.

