### Outcome assessment

Outcome data will be collected via online survey which will include self-measurement of height, weight, and waist circumference; a 24-h dietary recall collected via the Automated Self-Administered 24-h Dietary Assessment Tool (ASA24) [95]; and self-reported pedometer or wearable fitness tracker readings. Survey data will be collected using the Qualtrics application. All data will be coded using participant identification numbers instead of participant names. Only the Principal Investigator and the research staff will have access to the list that matches the names with the participant identification number. Data will be stored in a secure central location and access to files will be restricted to specific study staff. The contents of identifiable data files will be encrypted to secure data. SimpleStep Rechargeable Step Counters (Pedometer Express_,_ Cedar Minnesota, USA) or a wearable fitness tracker owned by the participant (e.g., Fitbit) will be used to obtain objective data on participant PA. The participant-owned fitness tracker must be comparable to the pedometer provided by the project (e.g., 3D motion sensor). Pedometers will be worn for seven days at each time point. Participants will record their daily steps and then report them to attain valid and reliable estimates of participants’ average daily PA.

LS7 score at 24-month follow-up is the primary efficacy endpoint. LS7 is a 7-item composite cardiovascular health score correlated with prevalence of cardiovascular disease events [96, 97]. Each item is classified as poor (0), intermediate (1), or ideal (2) (see Table 3). Scores for each of the seven items are summed for a total LS7 score between 0 and 14, with higher scores indicating better health.

**Table 3 Tab3:** American Heart Association’s Life’s Simple 7 components and scoring

Indicator	Poor (0)	Intermediate (1)	Ideal (2)
Smoking	current smoker	quit < 12 months ago	never smoked or quit > 12 months ago
BMI	obese (> 30)	overweight (25–29.9)	healthy weight (< 25)
Physical activity	none	some (1–149 min/week of moderate or 1–74 min/week of vigorous)	recommended amount (≥ 150 min/week of moderate or ≥ 75 min/week of vigorous)
Healthy diet indicators met • ≥ 4.5 cups/day of FV • ≥ 2 servings/week of fish • ≥ 3 servings/day of whole grains • ≤ 36 oz/week of sugar‐sweetened beverages • ≤ 1500 mg/day of sodium	0 or 1 indicators	2 or 3 indicators	4 or 5 indicators

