**Secondary outcomes—individual**						
BMI^a^	Self-measured		X	X	X	X
Waist circumference (in)	Self-measured		X	X	X	X
High/elevated blood pressure (y/n)^a^	Classified from self-reported measurements, diagnosis, and medication use		X	X	X	X
High/borderline total cholesterol (y/n)^a^	Classified from self-reported measurements, diagnosis, and medication use		X	X	X	X
Diabetes/pre-diabetes (y/n)^a^	Classified from self-reported measurements, diagnosis, and medication use		X	X	X	X
General health status	SF-36 general health item [105]		X	X	X	X
Current smoker (y/n)^a^	LS7 item [103, 104]		X	X	X	X
Total HEI score (1–100)	Single 24-h recall collected via the ASA24 [95]		X	X	X	X
Total fruit and vegetable intake (cups/day)^a^	LS7 item [103, 104]; ASA24 [95]		X	X	X	X
Consumption of whole grains (servings/day)^a^	LS7 item [103, 104]; ASA24 [95]		X	X	X	X
Fiber intake (g/day)	DSQ [106, 107]; ASA24 [95]		X	X	X	X
Met recommendation for fish consumption (y/n)^a^	LS7 item [103, 104]		X	X	X	X
Consumption of ultra-processed foods (% total kcal)	ASA24 [95]		X	X	X	X
Frequency of consuming ultra-processed foods (times/month)	Adapted from DSQ [106] and BSQ2 (9 items) [108]; ASA24 [95]		X	X	X	X
Red and processed meat consumption (g/week)	Estimated from DSQ [106, 109]; ASA24 [95]		X	X	X	X
Alcohol consumption (drinks/day)	Adapted from the AUDIT (2 items) [110]; ASA24 [95]		X	X	X	X
Total steps per day	Average of self-reported pedometer or wearable fitness tracker readings		X	X	X	X
Total physical activity (MET-min/week)^a^	IPAQ-long [111]		X	X	X	X
World Cancer Research Fund/American Institute for Cancer Research recommendation adherence score (0–7)	Composite [112]		X	X	X	X
Healthy eating motivation (1–5)	Adapted Naughton & McCarthy Healthy Eating Motivation Scale (3-items) [113]		X	X	X	X
Confidence for healthy eating (1–5)	Adapted from Sallis Eating Habits Confidence Survey and Seguin-Fowler Expanded Eating Habits Confidence Survey (7-item) [114, 115]		X	X	X	X
Social support for healthy eating (1–5)	Ball Social Support for Healthy Eating Scale [116]		X	X	X	X
Exercise attitudes (1–5)	Adapted from Sect. 2, question 5 of the AARP Exercise Attitudes and Behaviors Survey (4 items) [117]		X	X	X	X
Exercise confidence (1–5)	Adapted from Sallis Exercise Confidence Survey (3 items) [115]		X	X	X	X
Social support for physical activity (1–5)	Ball Social Support for Physical Activity Scale [116]		X	X	X	X

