#### Outcome analysis

All continuous variables will be examined for normality and, if not met, outliers will be investigated and rectified, and variables will be transformed to improve the distributions or non-parametric tests will be used [134]. Univariate descriptive statistics for all variables will be examined for all sample members pooled. Missing data will be examined for missingness at random and imputed using hierarchical multiple imputation methods [135–137]. Baseline outcome measures will be summarized with means and standard deviations for each treatment arm separately. Comparisons across arms will be completed using Chi-square tests (binary and categorical variables), t-tests (continuous variables), or non-parametric tests when warranted. Change from baseline will be calculated for each outcome variable at each point in time. Change at 36 months relative to 24 months also will be calculated to examine behavior maintenance.

Mixed models will test for differences in change in outcomes 24 months post-baseline between intervention and control arms by modeling a change score with control for baseline value and including community as a random effect to reflect clustering of persons within community (the level at which random assignment will occur). For dichotomous outcomes (e.g., current smoker, met whole grain recommendation), variables will be analyzed as assessed at 24 months post baseline with control for baseline value, and community as random effect. Secondary endpoints analysis will be conducted similarly to test for 12-month and 36-month change from baseline in intervention relative to control, as well as 36-month change from 24-month to test for maintenance of any observed 24-month effects. All tests will be considered significant at p < 0.05 with two-tailed tests.

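### Masking is declared infeasible for all research staff, although those who score and clean the ID-coded data could be masked; the likely effect on LS7 is small and the fix is cheap

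*Protocol article*

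**What the plan says.** The masking statement is in Methods, Communities: "It is not feasible to conceal assignment to intervention or control from participants or research staff due to the nature of the design". The same sentence adds one safeguard: "field staff involved in intervention delivery will not be involved in assessing outcomes".

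Outcome assessment describes how the data arise. "Outcome data will be collected via online survey which will include self-measurement of height, weight, and waist circumference", together with a self-administered online dietary recall and step counts that participants report themselves. On identification it says "All data will be coded using participant identification numbers instead of participant names", and on the key to those numbers "Only the Principal Investigator and the research staff will have access to the list that matches the names with the participant identification number". The primary endpoint is fixed there too: "LS7 score at 24-month follow-up is the primary efficacy endpoint".

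Three places leave room for staff judgement:

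- Outcome analysis says that, where a continuous variable is not normal, "outliers will be investigated and rectified", and that a transformation or a non-parametric test is then chosen.
- Table 4 gives the source of the blood pressure, cholesterol and diabetes outcomes, all marked as Life's Simple 7 components, as "Classified from self-reported measurements, diagnosis, and medication use".
- Outcome assessment admits a participant's own fitness tracker if it is comparable to the study pedometer.

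**The concern.** The nature of the intervention explains why participants and facilitators cannot be masked. It does not explain why a person working on a coded file must know the arm. The protocol nevertheless puts all research staff under one infeasibility statement.

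The safeguard offered protects a step that hardly exists here. Participants measure and report their own outcomes, so little staff measurement is left to separate from delivery. What staff do is process the reports, and nothing stated keeps knowledge of the arm out of that processing.

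At stake is a small, avoidable tilt in the LS7 score and in secondary outcomes, in a trial where participants' own reporting already cannot be masked.

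**Working it through.** **1. Does the stated reason cover the staff who handle data?** Set Communities beside Outcome assessment. The first says that concealment from research staff is infeasible because of the design. The second has the data arriving by online survey under ID numbers. Two things would still reveal the arm: the community label, since communities are the randomised units, and the process questions put only to intervention communities (Table 5, footnote a). Both can be removed or recoded. Masked scoring and cleaning is therefore feasible on the protocol's own data flow.

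**2. Which discretionary steps can reach LS7?**

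| Step | Reaches LS7? |
|---|---|
| Outlier correction | Only if the corrected input crosses a Table 3 cut-off |
| Choice of transformation or test | Affects the analysis, not the score |
| Conflicting reports on blood pressure, cholesterol, glucose | Yes, where measurement, diagnosis and medication disagree |
| Own-tracker comparability | No; it feeds daily steps, which Table 4 does not mark as an LS7 component |

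Table 3 also has two small gaps: a BMI of exactly 30 and quitting smoking exactly 12 months ago fall in no category.

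**3. The protocol's figures for Change Club members (CCM).** Inputs from Sample size determination: 70 per arm, 10% attrition a year, ICC 0.025. Five communities per arm comes from Communities.

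- Retained at 24 months: 70 × 0.9 × 0.9 = 56.7 (stated 57)
- Cluster size: 57 / 5 = 11.4
- Design effect: 1 + (11.4 − 1) × 0.025 = 1.26
- Effective n: 57 / 1.26 = 45.2 (stated 45)
- Detectable effect at 80% power, two-sided 5%: 0.597 SD by t-test (stated 0.60)

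The line reproduces. Since 0.60 SD is put at about 1 LS7 unit, the implied SD is 1 / 0.60 = 1.67.

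**4. What could arm-aware edits do in CCM?** Assume k net one-point LS7 edits, all in one direction, in one arm of 57.

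- SE of the difference: 1.67 × √(2/45) = 0.351
- Shift in standard errors: d = (k/57) / 0.351
- Two-sided type I error: Φ(−1.96 − d) + 1 − Φ(1.96 − d)

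| k | Shift, LS7 units | d | Type I error |
|---|---|---|---|
| 0 | 0 | 0 | 5.0% |
| 3 | 0.05 | 0.15 | 5.3% |
| 6 | 0.11 | 0.30 | 6.0% |
| 11 | 0.19 | 0.55 | 8.5% |

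**5. What would a larger tilt need in friends and family?** Retained per arm: 560 × 0.8 × 0.8 = 358; effective n 252 as stated. In SD units the SE is √(2/252) = 0.089. A tilt of 0.05 SD would give a type I error of 8.7%, and 0.10 SD would give 20.2%. With an SD of 1.67, these tilts need 0.05 × 1.67 × 358 ≈ 30 and 0.10 × 1.67 × 358 ≈ 60 net one-point edits, all in one direction and in one arm.

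**The case against.** The strongest reply is that the sentence is about running the trial, and that masked cleaning and database lock are usually left to an analysis plan or full protocol, neither of which is shown. That would answer a complaint about silence. Here the article states that masking research staff is infeasible, and its reason does not cover everyone it names. What stands of the reply is that the document never says that scorers or analysts will work with the arm in view. A reader might infer that arm-aware staff will make these decisions; the text leaves this open but does not say it.

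A second reply is that LS7 leaves little to judge. It is a sum of seven items scored 0, 1 or 2 by listed cut-offs, with medication rules written into Table 3, and most of it can be coded as an algorithm. Outcome analysis also has the descriptive statistics examined with all sample members pooled. This largely stands and is why the effect is small. It does not dispose of the point: no order of precedence is given where the self-reported sources conflict, correcting outliers is open-ended, and pooled descriptives do not mean that the arm is hidden.

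A third reply is that unmasked participants report almost everything themselves, so the larger bias is untouched. That is correct, and masking data staff should not be presented as a remedy for it.

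Finally, masking everything up to the analysis would do harm. With 20% attrition a year, 1 − 0.64 = 36% of friends and family and of residents would be missing at 24 months. Values imputed without arm carry no arm difference except what the community codes recover, which pulls the estimated effect towards zero. This stands, and it sets the limit of the fix.

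**Conclusion.** The point holds in a limited form. The infeasibility statement is broader than its reason allows, and staff who score and clean the data could be masked.

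The likely effect on LS7 is small: about 5.3% to 6.0% type I error for three to six net one-direction edits among CCM. These figures assume normal theory, the implied SD of 1.67, the stated effective sample size and one-point edits that do not cancel. The number of edits is illustrative; the protocol gives no basis for it.

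A reader might infer a false-positive rate of 9% to 20% in friends and family. The documents do not support that. It rests on an assumed tilt of 0.05 to 0.10 SD, which would take about 30 to 60 uncancelled edits in one arm of a score mostly set by fixed cut-offs. Nor does the tracker decision threaten the primary outcome, since it bears only on the secondary steps outcome. This is a worthwhile improvement, not a threat to the trial's validity.

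**What to change.** 1. In Communities, limit the infeasibility statement to participants and delivery staff (facilitators and field staff).
2. State that LS7 scoring, outlier handling, classification of conflicting self-reports, tracker decisions and the choice of transformation or test are completed and locked before arm is merged. They should be done on a file without arm, with scrambled community codes and without the intervention-only process items.
3. State that imputation and the final model checks follow the lock, with arm and community included, by code fixed in advance.

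The cost is a few sentences and one extra data-management step by existing staff. Because research staff hold the linking list, the member who strips and recodes the file should not be the one who then scores and cleans it. The change does nothing about bias from participants' own unmasked reports, and the protocol should not suggest that it does.
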